**Table 2 T2:**
[figure not shown]
Schedule for the treatment and the outcome measurements.

The primary outcome is the mean change in the VAS score for back and/or leg pain at 4W compared with baseline. The baseline VAS score will be measured immediately before the first intervention. The subject will indicate the degree of back and/or leg pain on a straight line of 100 mm. On that line, the left endpoint, 0, is no pain, and the right endpoint, 100, is the maximum pain imaginable.^[18]^

The secondary outcomes include back and/or leg pain at other time points, the clinical relevance^[19–22]^, dysfunction of the lumbar spine, range of motion of the lumbar spine, quality of life, and global assessment.

The clinical relevance will be assessed by comparing the percentage of subjects who indicate an improvement of more than 15 mm on the VAS, which corresponds to the Minimal Clinically Important Difference (MCID), of more than 30%, and of more than 50% between the 2 groups. In 2008, a consensus statement was issued that recommended MCID values for chronic pain assessment tools (pain, dysfunction, psychological factors, quality of life, etc.). According to a study that investigated the clinical relevance of the VAS for chronic back pain, the MCID was found to be greater than 15 mm based on the VAS (0–100 mm). Thus, in this study, we compare the proportions of subjects who have a decrease in the VAS score of 15 mm in each of the 2 groups. According to the above recommendation, in assessments using the VAS or the NRS, reductions of more than 30% and 50% in the MCID in chronic pain research suggest moderate clinically important changes and substantial improvements, respectively. Therefore, the main assessment tool of this study will be the VAS, so we will use it according to the criteria of the above recommendations.

The dysfunction of the lumbar spine will be assessed by using the mean changes in the scores on the Korean version of the Roland Morris Disability Questionnaire (RMDQ)^[23–26]^ at 2W, 4W, and 6W compared with baseline. The RMDQ was designed to measure the physical dysfunction of patients with back pain. Twenty-four questionnaire items will be simply answered “Yes (1) / No” (0), and the questionnaire will be scored from 0 to 24. A higher score indicates a greater degree of dysfunction. This survey has 2 advantages: the respondents can quickly complete the survey and the survey is easy to apply.

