The range of motion of the lumbar spine will be assessed by using the mean changes in the measured values on the Modified-Modified Schober Test (MMST)^[27,28]^ at 2W, 4W, and 6W compared with baseline. The MMST is a physical examination that assesses lumbar vertebrae mobility. With the subject standing straight, the end points 10 cm above and 5 cm below a straight line based on the point where the mid-line of the vertebrae and the connection-line of both Posterior Superior Iliac Spines meet will be marked. Then, the researching physician will let the subject bend his or her lower back forward to the maximum extent while still feeling no pain and will then measure the amount of change in the distance between the 2 points.

The quality of life will be assessed by using the mean changes in the scores on the Korean version of the EuroQol Five Dimensions questionnaire (EQ-5D)^[29,30]^ at 2W, 4W, and 6W compared with baseline. The EQ-5D is the most widely used tool for measuring quality of life. Hence, only the EQ-5D Index will be used in this study.

The global assessment will be done by using the Patient Global Impression of Change (PGIC)^[31]^ at 4W. The PGIC is a method for assessing the alleviation of the symptoms that the subjects have felt themselves before and after treatment. The subjects are able to choose from 7 categories of responses to how much the back and/or leg pain has been reduced compared with before their participation in this study.

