### Statistical analysis

2.8

The data obtained from the subjects of this study will be analyzed in the form of a full analysis set (FAS) analysis group and a per protocol (PP) analysis group. The FAS analysis group refers to analyzing a set of subjects that minimizes those who are excluded, except for a legitimate reason, from the analysis among the randomly assigned subjects. The PP analysis group refers to analyzing a set of subjects who have participated in more than 75% of the interventions (3 or more interventions) specified in this study's protocol and have not violated this study's protocol, and for whom the assessment variables have been measured completely. Both the FAS analysis group and the PP analysis group will be used for the effectiveness analysis while the main analysis group will be the FAS analysis group and the auxiliary confirmation will be performed by using the PP analysis group.

All statistical analyses will be conducted using the 2-tailed test in principle, and the significance level will be set at 5%. Analyses will use the statistical program SAS Version 9.4 (SAS Institute, Inc, Cary, NC). When missing values are encountered, they will be processed using multiple imputations.

The descriptive statistics of the subjects’ demographic characteristics and clinical baseline variables, such as gender, age, history, and drug dosage, will be presented for each treatment group. If the comparisons between the 2 groups involve continuous data, the mean and the standard deviation will be presented, and analyses will be performed using the independent *t* test or the Wilcoxon rank sum test. As needed, the 95% confidence interval will be provided. If the comparisons between the 2 groups involve categorical data, the frequency and the percentile will be presented, and analyses will be performed using the chi-square test or the Fisher exact test.

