The primary outcome variable is the mean changes in the score on the VAS at 4W compared with the baseline and will be analyzed using an analysis of covariance with the covariates being the VAS score at baseline and the fixed factor that in each treatment group. Secondary outcome variables will be analyzed in the same manner as the primary outcome variable. If the outcome variables are categorical data, they will be analyzed using the chi-square test or the Fisher exact test. If necessary, a paired *t* test or Wilcoxon signed-rank test will be used for the primary and the secondary outcome variables to analyze differences in measured values before and after treatment in each group, and a repeated measures analysis of variance will be performed to test the difference in the trend at each visit. The Dunnett procedure will be used for multiple comparisons.

If necessary, subgroup analyses of outcome variables, such as demographic variables measured at baseline (e.g., gender, age, duration of illness, treatment expectancy, etc.), whether or not rescue medicines were taken, the amounts of rescue medications taken, the hospital at which the subject was treated, etc., may be conducted. The safety assessments will primarily be performed by analyzing the frequency of adverse events and SAEs that the researchers suspect to be associated with treatment. The collected safety data will be appropriately summarized. All adverse events that occur will be listed with a detailed description. All SAEs will be recorded descriptively. Adverse events will be collected through patient symptom reports and researcher observations. The frequency of each adverse event associated or not associated with intervention will be recorded and analyzed using descriptive statistics. No interim analysis will be performed.

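### Section 2.8 most naturally sends the seven-category PGIC to a chi-square or Fisher test, which is valid but ignores the category order and loses power for a shift toward improvement

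*Protocol article*

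**What the plan says.** Section 2.6 of the protocol article lists the secondary outcomes, ending with "dysfunction of the lumbar spine, range of motion of the lumbar spine, quality of life, and global assessment". The global assessment is the PGIC, scheduled at 4 weeks only. Of the scale the article says: "The subjects are able to choose from 7 categories of responses to how much the back and/or leg pain has been reduced". The answers are thus graded by amount of improvement.

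Section 2.8 offers two routes for a secondary outcome:

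- the general one: "Secondary outcome variables will be analyzed in the same manner as the primary outcome variable", that is, ANCOVA of the change with the baseline value as covariate;
- the exception: "If the outcome variables are categorical data, they will be analyzed using the chi-square test or the Fisher exact test".

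The same section gives a matching rule for group comparisons in general. For categorical data, "analyses will be performed using the chi-square test or the Fisher exact test". The Wilcoxon rank sum test appears only in the sentence that begins "If the comparisons between the 2 groups involve continuous data, the mean and the standard deviation will be presented". The article names no method for ordered categories and no responder cut for PGIC.

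**The concern.** PGIC asks a directional question: do patients in one arm report more improvement than those in the other? A chi-square or Fisher test on seven columns asks whether the two patterns differ in any way. Its p-value would be the same if the seven answers were shuffled, so it spreads its sensitivity over six directions of difference when one is of interest. It also yields no effect estimate.

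At stake is the trial's only patient-rated global outcome. A consistent shift toward improvement could be reported as not significant when an ordered test on the same data would have detected it. Leaving the method open until the data are seen would also invite a choice between tests after the fact.

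**Working it through.** **1. Which route applies to PGIC.** The ANCOVA needs a baseline value and a change from it. PGIC has neither, so that route is closed as written. Section 2.6 describes PGIC as categories, and section 2.8 has one rule for categorical outcomes. PGIC is also the only efficacy outcome with more than two categories; the VAS responder outcomes (more than 15 mm, 30% and 50%) are binary and suit the rule.

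**2. The plan's own sample size (section 2.3), reproduced.** Inputs: difference 15, SD 24.71, two-sided 5%, power 90%, 1:1, dropout 20%.

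n = 2(1.960 + 1.282)² × 24.71² / 15² = 57.03, rounded up to 58 per arm. 58 / 0.80 = 72.5, rounded up to 73 per arm and 146 in total, as stated. The PGIC calculations below mainly use 58 per arm, the number expected to complete. The article claims no power for PGIC.

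**3. Cost of extra degrees of freedom.** For an ordered 1-df test at two-sided 5%, the noncentrality is λ = (1.960 + z_power)²:

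- 80% power: λ = (1.960 + 0.842)² = 7.85
- 90% power: λ = (1.960 + 1.282)² = 10.51

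Power of a chi-square test at the same λ:

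| df | where 1 df gives 80% | where 1 df gives 90% |
|---|---|---|
| 6 (full 2x7 table) | 52% | 67% |
| 3 (four categories in use) | 64% | 78% |

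To recover 80% (90%) power with 6 df, λ must be 13.62 (17.42). That is 13.62 / 7.85 = 1.74 (17.42 / 10.51 = 1.66) times as many patients.

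**4. Simulation with common odds ratios.** The documents give no PGIC distribution or effect, so both are assumed. The control distribution from best to worst is 5, 15, 30, 25, 15, 7 and 3%, with 58 per arm and two-sided 5%.

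| Common odds ratio | Chi-square 2x7 | Wilcoxon rank sum | Loss (points) |
|---|---|---|---|
| 2.0 | 27% | 54% | 27 |
| 2.5 | 46% | 78% | 32 |
| 3.0 | 65% | 91% | 26 |

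Repeat runs differ by a point or two, so the loss is about 25 to 32 points. With 73 per arm and an odds ratio of 2.5, the figures are 59% and 87%.

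**5. Sensitivity to the assumed distribution.** Here the effect is tied to the protocol's VAS design effect, 15 / 24.71 = 0.607 SD, applied as a shift on an underlying normal scale over four different control distributions. At 58 per arm, chi-square has 59 to 61% and Wilcoxon 85 to 87%. At 0.4 SD they have 25 to 27% and 51 to 54%. Fisher's exact test, checked at 58 per arm for two of these distributions, has 61 to 63% at 0.607 SD, so it loses about as much.

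**6. Collapsing.** If the same chi-square rule is applied to PGIC split into the best three answers against the rest, power at odds ratio 2.5 and 58 per arm is about 66%. The loss against Wilcoxon is then 78 − 66 = 12 points, not 32.

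**7. Type I error.** With no difference between arms, the 2x7 chi-square test rejects in about 3 to 5% of simulated trials.

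**The case against.** The strongest objection is that the article never assigns a test to PGIC. The categorical rule is correct for the VAS responder outcomes and may have been written for them. PGIC could be scored 1 to 7 and compared by the t test or rank sum test, or dichotomised, and a condensed article may leave that to an analysis plan. This stands in part: that the rule covers PGIC is an inference. It is a strong one, because the article calls the answers categories, the ANCOVA cannot apply, and the rank sum test is named only for continuous data. The point is therefore a stated rule that fits badly, not a missing detail.

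Second, the size of the loss rests on assumed distributions and an uncollapsed table. That stands; collapsing reduces the loss but does not remove it. The loss also concerns a shift in one direction. For a difference that is not a consistent shift, chi-square need not lose.

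A reader might also infer more than the documents support:

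- **That the test is invalid.** It is not; its size is held, and a significant result from a pattern other than improvement is not a type I error.
- **That sparse extreme categories are a separate defect.** Few answers there are likely, but Fisher's exact test is named in the same rule and deals with that.
- **That direction would be invisible.** Section 2.8 has group frequencies presented for categorical comparisons, so a reader could see it. Only a formal effect estimate is lacking.
- **That the model must adjust for hospital.** That is a separate matter from the order of the categories.

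**Conclusion.** The point holds as one of efficiency in a secondary outcome. Read in the most natural way, section 2.8 gives PGIC a valid test that discards the order of its categories. On the full table, power falls from 80% to about 52%, or from 90% to about 67%. In the simulated cases with 58 per arm and odds ratios of 2 to 3, the loss is about 25 to 32 points.

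These figures assume that the rule covers PGIC, that all seven categories are kept, that the true difference is a shift in one direction, and that the assumed answer distributions are reasonable. The analytic comparison in step 3 needs no answer distribution, only equal noncentrality for the two tests. The VAS primary analysis, the 73 per arm and the safety analysis are untouched, so it would be wrong to read this as a threat to the trial's main conclusion.

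**What to change.** Add one sentence to section 2.8: PGIC at 4 weeks is compared between groups as an ordinal outcome by the Wilcoxon rank sum test. Stratifying it by sex, the randomisation stratum (van Elteren test), is optional. If an effect estimate is wanted, give the common odds ratio with 95% confidence interval from a proportional-odds model. Limit the chi-square or Fisher rule to the binary VAS responder outcomes and other unordered categories.

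The cost is that one sentence, settled before anyone analysing the data sees results by group. Data collection and sample size do not change. The small downside is that the odds ratio depends on the proportional-odds assumption; the rank sum test remains a valid test of no difference without it.

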### Sample size calculation

2.3

Based on the results of a pilot study and clinical significance, we assume that the mean difference (δ) between the changes in the VAS before and after treatment in each group is 15 and the standard deviation (σ) is 24.71. When a significance level of 5%, a power of 90%, and an assignment ratio of the groups of 1:1 are applied, the number of subjects in each group (n) is given by^[14]^ 

Also, for an expected dropout rate of 20%, according to 

at least 73 subjects per group are required, for a total of 146 subjects.

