### Outcome measures

2.6

Assessments will be conducted at baseline and at 2 weeks (2W), 4 weeks (4W), and 6 weeks (6W) after randomization. The assessments at baseline and 2W during the intervention period will be performed before the assigned intervention for that visit. The schedule for the assessments of the results is shown in Table 2.

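### The optional repeated measures ANOVA names no baseline covariate and does not itself estimate the arm difference at any visit; a baseline-adjusted mixed model would be a clearer and somewhat more efficient supporting analysis

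*Protocol article*

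**What the plan says.** Under Outcome measures (2.6), the protocol article states: "Assessments will be conducted at baseline and at 2 weeks (2W), 4 weeks (4W), and 6 weeks (6W) after randomization". VAS pain at visits other than 4W is a secondary outcome, and RMDQ, MMST and EQ-5D are defined as mean changes from baseline at 2W, 4W and 6W.

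Under Statistical analysis (2.8), the primary outcome is to be "analyzed using an analysis of covariance with the covariates being the VAS score at baseline", with treatment group as the fixed factor. Secondary outcomes are to be handled the same way. A conditional sentence, to apply if needed, then adds within-group paired tests and says that "a repeated measures analysis of variance will be performed to test the difference in the trend at each visit". The Dunnett procedure is named for multiple comparisons. The section does not say whether baseline is one of the repeated levels, which term of the ANOVA is to be read, whether a baseline covariate is included, or what Dunnett compares.

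**The concern.** This is the only planned test that uses all visits of an outcome together, and its stated aim is unclear. A trend is a pattern across visits, so there is no trend at a single visit. The group-by-visit term answers one overall question and supplies no estimate or interval for any visit.

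The answer also depends on a choice left open. On post-baseline changes, the group-by-visit term asks only whether the arm difference varies over 2W, 4W and 6W. A steady advantage for acupotomy would then be reported as no difference in trend, and a reader could take that as contradicting a positive 4W ANCOVA. With baseline as a level, the term does test for a treatment effect, but it uses baseline less efficiently than the ANCOVAs planned beside it.

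At stake are the clarity and precision of a supporting analysis, not the trial's main conclusion.

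**Working it through.** **Inputs from the protocol (2.3 and 2.8).** "we assume that the mean difference (δ) between the changes in the VAS before and after treatment in each group is 15" (mm); "the standard deviation (σ) is 24.71", read here as the SD of the change; "a significance level of 5%, a power of 90%, and an assignment ratio of the groups of 1:1 are applied"; two-sided tests; 20% dropout; 73 per group.

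**The plan's own figure.** n = 2 × (24.71/15)² × (1.960 + 1.282)² = 57.03, so 58 per group. 58/0.8 = 72.5, so 73 per group and 146 in total. This matches the protocol. Power at 58 per group is 90.0% by the t distribution (90.5% by the normal approximation).

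**Assumptions that the protocol does not supply.** 58 analysable subjects per arm; equal SD at all visits; the same correlation ρ between any two visits (compound symmetry), from 0.2 to 0.8; and the effects at 2W and 6W. Two profiles are used: a constant 15 mm, and 6/10/10 mm at 2W/4W/6W. Compound symmetry favours the repeated measures ANOVA, since sphericity then holds.

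**Case A: ANOVA on changes at 2W, 4W and 6W.** Noncentrality λ = n × Σ(d − d̄)² / 24.71², with 2 and 228 df.
- Constant 15 mm: Σ(d − d̄)² = 0, so λ = 0 and the rejection rate is 5%, whatever ρ is.
- 6/10/10 mm: d̄ = 8.67 and Σ(d − d̄)² = 10.67, so λ = 58 × 10.67/610.6 = 1.01 and power is 13%.

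**Case B: ANOVA with baseline as a fourth level.** Same formula with d = 0 at baseline, on 3 and 342 df. Randomization makes the arms equal in expectation at baseline, so the null is no arm difference at any of the three later visits.
- Constant 15 mm: d̄ = 11.25 and Σ(d − d̄)² = 11.25² + 3 × 3.75² = 168.75, so λ = 16.03 and power is 93.2%.
- 6/10/10 mm: d̄ = 6.5 and Σ(d − d̄)² = 67, so λ = 6.36 and power is 54.0%.

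**Comparator for case B: a baseline-adjusted joint test of the same 3-df null.** After adjustment for baseline, the covariance of the three visits is σ²(1 − ρ)(I + ρJ). With 2σ²(1 − ρ) = 24.71², λ = n × [Σd² − ρ/(1 + 3ρ) × (Σd)²] / 24.71², on 3 and 111 df.

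| Profile | ρ | Bracket | λ | Adjusted power | ANOVA power | Loss (points) |
|---|---|---|---|---|---|---|
| 15/15/15 | 0.2 | 675 − 0.125 × 2025 = 421.9 | 40.1 | 100% | 93.2% | 7 |
| 15/15/15 | 0.5 | 675 − 0.200 × 2025 = 270.0 | 25.6 | 99.3% | 93.2% | 6 |
| 15/15/15 | 0.8 | 675 − 0.235 × 2025 = 198.5 | 18.9 | 96.1% | 93.2% | 3 |
| 6/10/10 | 0.2 | 236 − 0.125 × 676 = 151.5 | 14.4 | 89.4% | 54.0% | 35 |
| 6/10/10 | 0.5 | 236 − 0.200 × 676 = 100.8 | 9.6 | 72.4% | 54.0% | 18 |
| 6/10/10 | 0.8 | 236 − 0.235 × 676 = 76.9 | 7.3 | 59.3% | 54.0% | 5 |

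**Sensitivity to the SD reading.** If 24.71 were the SD of a single score, σ² = 24.71² and both λ become (n/2) × [..]/(24.71²(1 − ρ)). At a constant 15 mm, the powers are then 75.7% against 99.2% at ρ = 0.2 (24 points), 93.2% against 99.3% at ρ = 0.5 (6 points), and essentially 100% for both at ρ = 0.8.

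**Does Dunnett fill the gap?** With two arms there is no set of treatments to compare with a control. Dunnett can only compare visits with a reference visit, which is not an arm difference by visit.

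**The case against.** The strongest reply is that the test is conditional and supporting, and that the plan already answers the by-visit question. A reader might infer that arm differences at 2W and 6W are unavailable. They are not: VAS at other time points and the changes in RMDQ, MMST and EQ-5D are secondary outcomes, and these receive the baseline-adjusted ANCOVA. A steady benefit would show there. This stands in full.

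Second, on post-baseline changes a constant benefit is truly no difference in trend, so a 5% rejection rate is correct behaviour under a true null. The arm-by-visit term of a mixed model would behave the same way. This also stands: what a mixed model adds is the reported differences at each visit and on average, not a better interaction test.

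Third, the lack of baseline adjustment is read from silence in a condensed article, and with baseline as a level the interaction already works on change from baseline. That is fair as to intent. Even so, case B shows that using baseline as a level recovers less than adjusting for it.

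A reader might also press sphericity and pooling of F tests after multiple imputation. Both are weak: corrections and pooling are details that an article may leave to the analysis plan, and simulated type I error without correction was only 5.2 to 6.6%.

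**Conclusion.** The point holds as a minor improvement to a supporting analysis. The wording leaves the tested hypothesis open. Under one reading, a constant benefit appears as no difference in trend; under the other, power is lost against a baseline-adjusted test of the same null. That loss is about 3 to 7 points at a constant 15 mm with a change SD of 24.71, and about 5 to 35 points under the assumed 6/10/10 mm profile, at 58 per arm and ρ from 0.2 to 0.8.

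A reader might infer a single or maximum power loss, for example one in the high twenties. The protocol does not support that: it gives no between-visit correlation and no effect at 2W or 6W, and the loss moves over the whole range above as these change. Nor may a 1-df average difference be set against a trend test as if both asked the same question.

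The 4W primary ANCOVA, the sample size and the by-visit secondary ANCOVAs are unaffected.

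**What to change.** Replace the repeated measures ANOVA with a mixed model for repeated measures on change at 2W, 4W and 6W. Include arm, visit, arm-by-visit, baseline value and baseline-by-visit, with an unstructured within-subject covariance. Report the arm difference with its 95% CI at each visit and averaged over visits, and label the model as supporting the 4W ANCOVA.

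If the ANOVA is kept, state at least whether baseline is a repeated level, which term is tested, when the analysis will be run, and what the Dunnett procedure compares.

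The cost is one sentence of wording and a few more covariance parameters (six for three visits), which 146 planned subjects support easily. The SAS version already named can fit the model, and no new data are needed.

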#### Cointerventions

2.5.3

All subjects will be instructed not to receive any treatment for back and/or leg pain, except for the treatments we provide. During the period of participation in the clinical trial, they will receive rescue medication (i.e., acetaminophen, up to 3000 mg per day). They will be instructed to take the rescue medicine only when their back and/or leg pain is so severe that it is unbearable. At each visit, the clinical research coordinator (CRC) will accurately record on the CRF the total rescue medication dosage used by the subject since the last visit.

At the discretion of the researching physician, all subjects will be allowed to continue to take medications that they were taking before their participation in this study. The subjects will be instructed to report to the researcher at each visit any changes in the dosages of the medications that they have been taking or any new medications that they have taken since they began participating in this study. They will also be instructed not to take arbitrarily a drug that might affect the study's outcomes. If the subject does not follow the above instructions and if the principal investigator (PI) judges that those actions could significantly influence the study's outcomes, that subject will be dropped from this study.

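### Optional subgroup analyses by rescue use and rescue amount condition on a post-randomisation response to pain, so their treatment comparisons are biased if the arm affects rescue use

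*Protocol article*

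**What the plan says.** Section 2.8 (Statistical analysis) permits subgroup analyses of the outcome variables. After naming baseline characteristics such as gender, age, duration of illness and treatment expectancy, it adds "whether or not rescue medicines were taken, the amounts of rescue medications taken" and hospital. The status is permissive: the sentence opens with a condition of necessity and closes with "the hospital at which the subject was treated, etc., may be conducted".

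Section 2.5.3 (Cointerventions) fixes what rescue use is:

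- **Timing:** "During the period of participation in the clinical trial, they will receive rescue medication".
- **Trigger:** patients are to use it "only when their back and/or leg pain is so severe that it is unbearable".
- **Recording:** at each visit the coordinator enters "the total rescue medication dosage used by the subject since the last visit".

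Section 2.6 (Outcome measures) defines the primary endpoint: "The primary outcome is the mean change in the VAS score for back and/or leg pain at 4W compared with baseline".

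**The concern.** The list puts rescue use beside gender and age as if it were the same kind of factor. It is not. Gender and age are fixed before allocation, so patients sharing a level are still randomised between arms. Rescue use is decided afterwards, by the patient, in response to pain.

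Suppose acupotomy works. Some patients whose pain would have driven them to rescue under manual acupuncture then manage without it. The acupotomy patients who still take rescue are those with a worse underlying pain course than the control patients who take it. Likewise, the acupotomy patients who avoid rescue include people with a worse underlying course than the controls who avoid it. In both strata acupotomy is compared with a prognostically better control group, and baseline VAS adjustment does not remove the difference because it arises after baseline.

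At stake is a table that a reader of an open-label pain trial would find natural: the effect in rescue users and in non-users. It could show a real benefit as smaller in both strata than overall, or show a difference where there is none.

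**Working it through.** **1. The plan's own figure.** Inputs from section 2.3: difference 15, SD 24.71, power 90%, 5% level; two-sided from section 2.8.

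n = 2 × (1.960 + 1.282)² × 24.71² / 15² = 57.03, so 58 per group. With 20% dropout, 58 / 0.8 = 72.5, so 73 per group and 146 in total. The stated size is reproduced; rescue plays no part in it.

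**2. When is there bias?** Two conditions are needed together: (a) rescue use shares causes with 4-week pain, and (b) the arm affects rescue use. The trigger in section 2.5.3 gives (a). Condition (b) is not stated, but follows if acupotomy lowers pain more, as section 2.3 assumes. Patients are unblinded (section 2.4), which is another possible route.

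**3. Size, hard trigger.** Assumptions not in the article: baseline VAS N(60, 15); mean control improvement 15 mm; 24.71 used as residual SD (section 2.3 gives it for change scores); error correlation 0.8 between interim and 4-week pain; rescue taken if interim pain exceeds 50 mm; constant true benefit 15 mm.

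Interim pain has SD √(15² + 24.71²) = 28.9. Control mean is 60 − 15 = 45 and acupotomy mean 45 − 15 = 30. Rescue rates are P(Z > 5/28.9) = 43% and P(Z > 20/28.9) = 24%.

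Baseline-adjusted regression within strata (2,000,000 simulated patients) gives the estimated benefit in mm:

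| Hard-trigger variant | No rescue | Rescue |
|---|---|---|
| Cut-off 50, correlation 0.8 | 9.6 | 7.2 |
| Same, correlation 0.5 | 11.6 | 10.1 |
| Same, correlation 0.3 | 13.0 | 12.1 |
| Same as first row, no control improvement (63% vs 43% rescue) | 8.1 | 8.6 |

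Varying the cut-off from 40 to 60 mm, or the control improvement from 0 to 20 mm, gives about 6 to 11 mm.

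**4. Size, gradual trigger.** A hard cut-off is severe. If the probability of rescue rises smoothly with pain (logistic, centre 50 mm, scale 10 to 30 mm), the estimates are:

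- correlation 0.8: 11.1 to 13.6 mm without rescue, 9.8 to 13.5 mm with rescue;
- correlation 0.5: 12.6 to 14.1 mm and 11.7 to 14.1 mm.

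A separate logistic model (70% of residual variance shared by interim and 4-week pain; slope per SD of pain) gives:

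| Slope | Rescue, acupotomy vs control | No rescue | Rescue |
|---|---|---|---|
| 1 | 37.5% vs 49.9% | 13.1 | 13.0 |
| 2 | 31.5% vs 49.9% | 10.9 | 10.2 |
| 2, less rescue overall | 14.3% vs 27.7% | 12.2 | 10.1 |

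**5. No true VAS effect, but the arm shifts rescue use.** In these models the selection error is additive, so it can be read off as 15 minus the stratum estimate: 15 − 9.6 = 5.4 and 15 − 7.2 = 7.8 mm (hard trigger); 15 − 10.9 = 4.1 and 15 − 10.2 = 4.8 mm (logistic, slope 2). Direct simulation gives the same values. If acupotomy lowers rescue use it looks worse by these amounts; if it raises rescue use it looks better (4.8 and 4.1 mm, logistic).

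**6. When the bias vanishes.** With rescue unrelated to pain, or with rescue balanced between arms, the estimates are 15.0 mm in both strata. With no effect on either VAS or rescue, they are 0.0 and 0.1 mm.

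**The case against.** The strongest reply is about weight. These analyses are optional and secondary. The primary analysis is an ANCOVA of the 4-week VAS change on arm and baseline VAS, with the full analysis set as the main set; nothing in it uses rescue, and no claim is tied to a subgroup result. That stands, and it keeps the point well short of a threat to the trial's main conclusion.

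Three stronger readings are tempting, and the article supports none of them.

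- **That every stratum estimate is bound to be biased.** This needs the arm to affect rescue use, which is the trial's hypothesis and not a given. Without it the bias is zero (step 6).
- **That the benefit would be cut by a third to a half.** The first row of the hard-trigger table gives (15 − 9.6)/15 = 36% and (15 − 7.2)/15 = 52%, but only with an all-or-nothing trigger, a 15 mm control improvement and a 50 mm cut-off that lies below the assumed mean baseline of 60 mm, an awkward match for unbearable pain. Gradual triggers leave a shortfall of about 1 to 5 mm.
- **That rescue is wrongly missing from the outcome list.** A condensed article may leave this to the full protocol or the analysis plan, so its absence is not an error.

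What the reply does not remove is the classification itself. The article names these factors outright, does not call the analyses descriptive, and gives no caution on reading them.

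**Conclusion.** The point holds in conditional form. Rescue use and rescue amount are post-randomisation variables driven by the pain under study, so they are unsuitable as subgroup factors for a treatment effect. If acupotomy changes rescue use, the within-stratum comparisons are biased. With a constant 15 mm benefit the illustrations run from about 6 to 14 mm; with no VAS benefit but an arm difference in rescue use, false differences of about 4 to 8 mm arise. Direction is stable: whenever acupotomy lowered rescue use, both strata were shifted against it. Size is not, because rescue rates, the sharpness of the trigger and the interim-to-4-week correlation are all assumed. Severity is minor to moderate.

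**What to change.** In section 2.8, delete the two rescue variables from the subgroup list and limit subgroup factors to those fixed before randomisation, meaning baseline variables and hospital.

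In their place, compare rescue medication between arms as randomised: any use, and total dose to 4 and 6 weeks. The dosage recorded at each visit is enough for this. It would not support a definition based on use close to the 4-week visit, because only the total since the previous visit is kept.

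The cost is a short wording change, one extra table, and the loss of an exploratory analysis that could not be read as a treatment effect.
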